## Methods: participants, interventions, and outcomes

### Study setting {9}

Male and female participants between the ages of 18 and 55 years at the time of enrollment are eligible for the study. The participants should be healthy as determined by their medical history, physical examination, and clinical verification by the investigator. All participants should have received at least 2 doses of an approved mRNA COVID-19 vaccine at least 4 months prior to enrollment. Participants will be enrolled at the Clinical Trial Unit at King Abdullah International Medical Research Center (KAIMRC), Kingdom of Saudi Arabia.

### Eligibility criteria {10}

#### Inclusion criteria

Potential study participants who meet ALL the following inclusion criteria will be eligible to participate in the study:

Male or female individuals between the ages of 18 and 55 years (inclusive) at the time of enrollment.Healthy individuals, as determined based on medical history, physical examination, and clinical verification by the investigator.Individuals who agree to commit to complying with planned scheduled visits, vaccination, laboratory tests, and any other procedures.Individuals who have received at least 2 doses of an approved mRNA COVID-19 vaccine at least 4 months prior to enrollment.Female subjects of childbearing potential must have used a highly effective contraceptive method for at least 60 days prior to receiving the first dose of the investigational vaccine and should continue using contraception for at least 1 month after Visit 5 (end of study). Post-menopausal female subjects with at least 12 months of amenorrhea (without an alternative medical cause) can be enrolled.Male subjects able to father children and sexually active with a female partner who is able to bear children must be willing to use (or have their female partner use) a highly effective contraceptive method from the time they receive the first dose of the study vaccine until at least 1 month after Visit 5.Individuals must be willing to sign the informed consent form (ICF), which includes all the requirements and restrictions listed in the ICF and the study protocol.

#### Exclusion criteria

Potential study participants who meet ANY of the following exclusion criteria will not be eligible to participate in the study:

Individuals with known infection with Hepatitis B virus (HBV), hepatitis C virus (HCV), or human immunodeficiency virus (HIV).Individuals currently infected and diagnosed with COVID-19 as documented by a PCR nasal swab test.Individuals who have received an mRNA-based COVID-19 vaccine within 4 months of first study drug administration.Individuals who have received only one dose of a COVID-19 vaccine.Individuals working in a facility with a high probability of SARS-CoV-2 infection, such as health workers in hospitals.Individuals with a history of severe allergic reactions and/or anaphylaxis and/or serious adverse reactions associated with vaccines and/or allergy or hypersensitivity to any component of the study intervention.Individuals using immunosuppressive therapy.Individuals receiving treatment or medications that can adversely affect the immune system in the 90 days before first investigational vaccine administration, including but not limited to: interferon, immunoglobulin, immunomodulators, epinephrine injectors, and cytotoxic drugs.Individuals diagnosed with any diseases or conditions that are associated with severe COVID-19, including the following factors:
Diabetes MellitusHypertensionAsthmaBMI more than 30 kg/m^2^Chronic pulmonary diseaseChronic liver diseasesChronic renal diseasesIndividuals with known or suspected immunological disorders, including autoimmune disease and diabetes mellitus.Individuals with current or previous neurological disorders, such as epilepsy or Guillain-Barré syndrome.Individuals with psychiatric disorders or cognitive impairment.Individuals with bleeding disorders or other conditions associated with prolonged bleeding time.Individuals with clinically significant abnormal safety laboratory results at screening, in the opinion of the investigator (retesting is allowed).Individuals receiving or planning to receive a non-study vaccine 30 days prior to study enrollment or during the study participation interval. Influenza vaccination is acceptable.Individuals receiving blood or donating blood or blood components 60 days prior to study enrollment or planning to receive or donate blood or blood components during the study.Individuals participating in a clinical trial (investigational vaccine, treatment, or device) 30 days prior to study enrollment or planning to participate in other clinical trials during the study.Individuals intending to participate in another clinical trial while enrolled in this study.Individuals with a positive alcohol or drug test or with a history of alcohol or drug addiction.Individuals with other health conditions that may compromise their health and safety while participating in the clinical trial or that may compromise the study's primary or secondary objectives, in the opinion of the investigator.Female participants who are pregnant, planning to become pregnant, or are breastfeeding.

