## Abstract

**Background:**

SARS-CoV-2 has been responsible for a worldwide public health crisis and a pandemic that began in February 2020, with approximately 679 million cases and over 6.7 million deaths to date. Despite the existence of approved COVID-19 vaccines, these vaccines are either based on mRNA technology or viral vectors. Imam Abdulrahman Bin Faisal University (IAU) has developed a thermally stable plasmid DNA (pDNA)-based vaccine candidate using a platform approach that enables the rapid development of vaccines against emerging viral diseases. The pDNA vaccine developed by IAU encodes the full-length, optimized version of the SARS-CoV-2 Spike protein. Key advantages of this pDNA vaccine are that it is cost-effective, thermally stable, and can be used to administer multiple immunizations without incurring anti-vector responses, making it a promising candidate as a vaccine booster dose.

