Confirm eligibility	X	X						
Collect prohibited medication use	X	X	X	X	X	X	X	X
Review hematology and chemistry results^c^	X	X	X	X	X	X		
Review temporary delay criteria		X						
Confirm use of contraceptives (if applicable)	X	X	X	X	X			
Obtain randomization number and study intervention allocation		X						
Collect blood sample for immunogenicity assessment^a^		~20 ml			~20 ml	~20 ml (optional 50 mL^d)^		
Administer study intervention^c^		X						
Assess acute reactions after study intervention administration^c^		X						
Explain participant communication methods (including for diary completion)		X						
Provide thermometer measuring device		X						
Provide diary to subjects		X						
Review reactogenicity diary data			X	X	X	X		
Review ongoing reactogenicity diary symptoms and obtain stop dates			X	X				
Collect diary to assess participant				X				
Collect AEs and SAEs as appropriate	X	X	X	X	X	X	X	X
Collection of COVID-19-related clinical and laboratory information							X	X

HBc Ab, hepatitis B core antibody; HBsAg, hepatitis B surface antigen; HCV Ab, hepatitis C virus antibody; HIV, human immunodeficiency virus; min, minutes; NAAT, nucleic acid amplification test; vax, vaccination.

^a^Availability of results will not delay further study activities.

^b^Two swabs will be taken at 1–2 days prior to Visit 1. One will be tested (at the site, if possible, otherwise at the central laboratory) within 48 h, and vaccination will only proceed if it is NAAT-negative for SARS-CoV-2 genomes. The second will be sent to the central laboratory for potential later testing.

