### Prior and concomitant medications {11d}

All prior and concomitant medications, vaccines, and blood products will be collected in the electronic case record form (eCRF). Concomitant therapy or treatment associated with SAEs should be collected in the eCRF from signing of the ICF until the end of the study. In addition, concomitant therapy associated with unsolicited AEs occurring from the time of day of vaccination (Visit1) until 21 days, should be collected and recorded in the eCRF. Concomitant medications associated with solicited AEs occurring from the time of vaccination until 7 days after vaccination should also be collected and recorded in the eCRF.

A subject receiving any of the following medications will be excluded from the study:

Statin medications up to 30 days of enrollment through the end of the study.Corticosteroids up to 30 days of enrollment. Inhaled and topical corticosteroids are permitted.Antimetabolite or alkylating drugs up to 30 days of enrollment through the end of the study.Treatments or medications that can adversely affect the immune system, such as interferon, immunoglobulin, immunomodulators, epinephrine injectors, cytotoxic drugs, and immune-modulating drugs, within 90 days of enrollment.Radiation therapy within 60 days of enrollment until the end of the study.Donating or receiving blood or plasma products up to 60 days of enrollment or planning to receive or donate blood and blood components throughout the study.Non-study vaccines up to 30 days prior to study enrollment until end of study with the exception of an influenza vaccine.

If a subject requires any treatment listed above or in the exclusion criteria, discontinuation of the subject from the study should be considered. The use of nutritional/herbal supplements or other medications such as antihistaminic drugs during screening and throughout the study period is not permitted. Subjects are permitted to use antipyretic drugs, such as paracetamol (up to a 1 g dose) for the treatment of any local or systemic reactions that can be associated with the study drug. Alternatively, a 500 mg dose of paracetamol can be taken every 6 h up to 36 h.

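### The 4-month washout covers only mRNA COVID-19 vaccines, so a recent vector or protein COVID-19 booster is caught only by the general 30-day rule and adds avoidable noise to the Day-30 fold rise

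*Protocol article*

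**What the plan says.** All of the following is in the Protocol article.

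- **Required background** (Inclusion criteria; repeated in substance under Study setting {9}): "Individuals who have received at least 2 doses of an approved mRNA COVID-19 vaccine at least 4 months prior to enrollment". There is no upper limit on doses and no restriction on the platform of a later dose.
- **COVID-19 vaccine washout** (Exclusion criteria): "Individuals who have received an mRNA-based COVID-19 vaccine within 4 months of first study drug administration".
- **Washout for other vaccines** (Exclusion criteria): "Individuals receiving or planning to receive a non-study vaccine 30 days prior to study enrollment or during the study participation interval". Section {11d} repeats it: "Non-study vaccines up to 30 days prior to study enrollment until end of study with the exception of an influenza vaccine".
- **Infection** (Exclusion criteria): "Individuals currently infected and diagnosed with COVID-19 as documented by a PCR nasal swab test". A footnote to Table 3 adds a swab shortly before dosing and says that "vaccination will only proceed if it is NAAT-negative for SARS-CoV-2 genomes". No interval since a past infection is listed.
- **Other platforms exist on the article's own account.** The Abstract says of the approved vaccines that "these vaccines are either based on mRNA technology or viral vectors", and the Discussion names recombinant protein vaccines.
- **Endpoints affected** (Immunogenicity endpoints and analysis): GMFR and the share of subjects with a 4-fold rise in binding antibody between Visit 1 and Visit 4, 30 days later. Interim analysis {21} uses the safety and immunogenicity data through Visit 4 to judge the dose for later trials.

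**The concern.** Two vaccines that present the same antigen are treated differently by platform, 4 months for mRNA and 30 days for everything else, and no reason is given. Platform-neutral wording was available: a neighboring exclusion, on having had only one dose, refers to any COVID-19 vaccine.

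A subject who received a spike vaccine a month or two before dosing may enter with a titer that is still changing. That subject's change from Visit 1 to Visit 4 then mixes the study vaccine with the earlier exposure. An upward drift looks like a booster response; a falling or high starting titer makes a 4-fold rise harder to reach. The stake is the clarity of the secondary immunogenicity results and of their contribution to dose choice. The primary safety endpoints are not shown to be affected. The article itself names low immunogenicity in humans as a weakness of plasmid DNA vaccines, so a modest signal has to be read against this noise.

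**Working it through.** The plan states no figure that depends on this rule, so there is none to reproduce. The check has two parts.

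**1. Does such a subject pass the listed criteria?** Take a subject with two mRNA doses well over 4 months ago and a vector or protein COVID-19 booster 31 days before enrollment.

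| Rule | Result |
|---|---|
| At least two mRNA doses, at least 4 months ago | met |
| mRNA vaccine within 4 months of first dosing | not triggered, because the booster is not mRNA |
| Only one COVID-19 vaccine dose | not triggered |
| Non-study vaccine in the 30 days before enrollment | not triggered, 31 > 30 |
| Current PCR-documented infection; NAAT before dosing | not relevant |

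The subject is eligible. The two washouts count to different dates, the mRNA rule to first dosing and the 30-day rule to enrollment. Screening is 0 to 28 days before Visit 1. If enrollment means screening, the booster lies 31 + 0 = 31 to 31 + 28 = 59 days before dosing, still well short of 4 months (about 4 × 30 = 120 days).

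**2. How far could one such subject move a result?** Inputs from the protocol: 14 subjects per cohort at 3:1, so 14 × 0.75 = 10.5 and 14 × 0.25 = 3.5, that is about 10-11 vaccine and 3-4 placebo. Assumed input, not in the documents: over the 30 days the background titer changes by a factor f between 0.5 (halving) and 4 (quadrupling), unrelated to study vaccine.

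A geometric mean over n subjects is multiplied by f^(1/n) when one of them carries the extra factor f:

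| Group size n | f = 0.5 | f = 4 |
|---|---|---|
| 10 (vaccine) | 0.5^(1/10) = 0.93 | 4^(1/10) = 1.15 |
| 11 (vaccine) | 0.5^(1/11) = 0.94 | 4^(1/11) = 1.13 |
| 4 (placebo) | 0.5^(1/4) = 0.84 | 4^(1/4) = 1.41 |
| 3 (placebo) | 0.5^(1/3) = 0.79 | 4^(1/3) = 1.59 |

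The ratio of GMFRs between two dose groups of 10 shifts by the same 0.93 to 1.15 if only one of them contains such a subject.

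For the 4-fold-rise proportion, a subject with f = 4 counts as a responder with no vaccine effect at all, which is 1/10 = 10 percentage points in a group of 10 and 1/4 = 25 points in a group of 4. A subject with f = 0.5 needs a vaccine-induced rise of 4/0.5 = 8-fold to be counted.

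**Chance imbalance.** Suppose a share p of enrollees is affected, with p from 0.05 to 0.30 (assumed; the documents give no figure).

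- At least one in a cohort of 14: 1 − 0.95^14 = 0.51 to 1 − 0.70^14 = 0.99.
- Vaccine and placebo shares differing by 20 points or more in a 10:4 cohort, from summing the two binomial distributions over all such outcomes: 0.19 to 0.53.

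**The case against.** The strongest reply is the concurrent randomized placebo. Each cohort is randomized and double-blind, and the immunogenicity objectives are framed against placebo. A reader might infer that the eligibility rule biases the vaccine-placebo comparison. It does not: background drift is balanced in expectation, and what remains is chance imbalance, which small arms suffer for any prognostic factor. This stands. It does not reach within-group GMFR, the 4-fold proportion, or comparisons between dose cohorts that are filled one after another and are not randomized against each other in time.

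A reader might also imagine a much larger distortion, for instance a subject still rising 10-fold, which would multiply GMFR by 10^(1/4) = 1.78 in a placebo group of 4. The documents do not support that. The protocol reads its own vaccine response at 30 days, and a subject boosted 31 days before enrollment is already past that point at Visit 1.

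Some safeguards exist. Section {11d} has all prior vaccines recorded in the eCRF, Table 3 collects non-study vaccine information at each planned visit, and Visit 1 titers are measured in everyone, so affected subjects could be described. Table 3 also lists temporary delay criteria at Visit 1, whose content the article does not give, and there is a discretionary exclusion for health conditions "that may compromise the study's primary or secondary objectives, in the opinion of the investigator". These may remove some subjects. None of them, as shown, sets an interval for a non-mRNA COVID-19 vaccine.

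Finally, the article does not state why 4 months was chosen. A settled immune background is a plausible purpose, but it is an inference, so the protocol cannot be said to fail an aim of its own.

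**Conclusion.** The point holds as a narrow, cheaply corrected weakness in a stated rule. As written, the 4-month exclusion leaves a non-mRNA COVID-19 booster subject only to a 30-day limit, and the article itself says such vaccines are approved. The consequence is avoidable noise in secondary immunogenicity summaries that, together with safety data, inform dose choice. It is not a bias in the average vaccine-placebo contrast.

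The illustrated size is a factor of 0.93 to 1.15 on GMFR in a group of 10 and 0.84 to 1.41 in a group of 4, for one subject with f between 0.5 and 4. Both f and the share of affected subjects are assumptions; if few such people present at this single center, the practical effect is small.

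Recent infection is a related but weaker matter. Only current PCR-positive infection is excluded, so a recently recovered, NAAT-negative subject meets the listed criteria. A reader might infer that the same 4 months should apply. No specific interval follows from the document, the delay criteria might partly cover the case, and an interval tied to documented infection would miss undocumented ones.

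**What to change.** In the mRNA exclusion criterion, replace the reference to mRNA-based vaccines by *any COVID-19 vaccine, whatever its platform*. Leave the 4 months, and its counting to first study drug administration, as they are. This uses the protocol's own threshold and leaves the 30-day rule in force for unrelated vaccines.

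For SARS-CoV-2 infection, the sponsor should decide whether to require an interval since documented infection and, if so, state it. If the temporary delay criteria already deal with recent infection or recent COVID-19 vaccination, a cross-reference from the eligibility list would be enough for that part.

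The cost is one reworded criterion by amendment, a few more screen failures and perhaps slightly slower recruitment of the 42 subjects. No procedure is added, and vaccine history is already collected.

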### Who will take informed consent? {26}

Prior to screening, each subject shall submit a signed consent indicating their agreement to participate in the study. The subject will be given a designated screening number that will be documented in the screening and enrollment log. The principal investigator is responsible for ensuring that informed consent is given by all potential study participants.

## Intervention

### Intervention description {11a}

The drug product is prepared using an aseptic fill and finish process and supplied in glass vials as a liquid for injection, where each dose will be filled in an individual glass vial according to the pDNA concentration in the study (1 mg, 2 mg, and 4 mg). The sponsor will be responsible for ensuring the correct labeling of the study vaccine in accordance with the legal and regulatory compliance at the study site where this Phase 1 study will be performed. The packing of the clinical batch will be up to 50 vials per carton. The drug product batch is stored at optimal temperature (-20°C) until usage. The sponsor will ensure the supply of the candidate COVID-19 pDNA vaccine to the designated study site according to GCP and Good Distribution Practice (GDP). The temperature monitoring device will be included per shipping container.

The investigational product, a vaccine, should be received at the designated study site by the investigator/designee. The study investigator/designee must ensure the following:

The vaccine is received at the appropriate temperature for shipment (-20°C) and verified by the downloaded data logger.The vaccine is received in good condition.The proper, temperature-appropriate storage of the vaccine in temperature-monitored freezers.The storage of the vaccine at a safe, secure, and locked location.Appropriate inventory and record documentation to ensure a proper storage temperature.

The storage of the investigational vaccine vials will be monitored by the study monitors during site visits. The unused investigational vaccine vials must be returned to the sponsor.

The investigational vaccine vials for this study will be stored at the appropriate temperature in a secure place under appropriate freezing conditions with temperature monitoring. The expiration date for the vaccine should be checked prior to vaccine administration to the subject. Expired vaccines MUST NOT be administered to the study subjects. If deviation occur the IMP must be immediately quarantine and labeled “Do Not USE”. The Sponsor should be notified within 24 h and the Sponsor shall review the temperature data and assess the impact of product quality. The IMP will either be released for use, destroyed, or returned to the Sponsor based on the investigation outcome.

Three dose levels of the COVID-19 pDNA vaccine vs. placebo will be tested in this study. Subjects will be randomized into three different dosing cohorts. In each cohort, 14 subjects will undergo the IM administration of vaccine or placebo (Saline) at a 3:1 allocation ratio. Subjects that are assigned to receive the vaccine will be administered at one of the following dose levels:

Cohort 1: 1 mgCohort 2: 2 mgCohort 3: 4 mg

Participants will be receiving the investigational vaccine or placebo at Visit 1 only. The dose is described in the IB. The study intervention will be administered IM, preferably in the deltoid muscle of the non-dominant arm. The liquid for injection will be withdrawn from the ampoule into a conventional syringe with a needle appropriate for IM administration, as described in the pharmacy manual. Administration of the vaccine should be performed by a qualified, GCP-trained member of study staff in accordance with the institutional and country-specific guidance. Standard vaccination practice should be observed and monitored.

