**Methods:**

This study aims to investigate the safety, tolerability, and immunogenicity of this prophylactic pDNA vaccine as a booster vaccine to protect against COVID-19 when administered as an intramuscular injection in a single ascending dose design. In total, 42 eligible healthy subjects will be enrolled in the study. The subjects will be randomized to receive either the investigational vaccine or placebo (Saline) at a 3:1 allocation ratio. Participants will have received two doses of a SARS-CoV-2 mRNA vaccine at least 4 months prior to enrollment. Subjects will be enrolled in a dose-escalating study and assigned to one of the three cohorts (Cohort 1: low-dose; Cohort 2: mid-dose; Cohort 3: high-dose). Primary endpoints will include local reactions and systemic reactions for up to 7 days following vaccination, adverse events from vaccination to 1 month, and serious adverse events from vaccination to 6 months. Secondary endpoints will include the evaluation of binding antibody (bAB) and neutralizing antibody (nAB) responses at vaccination day (Visits 1) and 30 days after vaccination (Visit 4), the ratio of bAB to nAB titers at Visits 1 and 4, and cellular immune responses (CD3, CD4, CD8, CD45RA, CCR7, IFN-γ, IL-2, IL-4, IL-13, and TNF) at Visits 1 and 4.

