### Trial Design {8}

This investigational vaccine study is a Phase 1, randomized, dose-finding, single-center study, enrolling healthy adults. In total, 42 healthy individuals will be enrolled in the study. The eligible individuals will be randomized to receive either the investigational vaccine or placebo (Saline). Subjects will be enrolled at a 1:1:1 ratio in a dose-escalating manner to one of three cohorts (Cohort 1: low dose level, “1 mg”; Cohort 2: mid-dose level, “2 mg”; Cohort 3: high-dose level, “4 mg”). All subjects will receive a single dose of the vaccine or placebo IM.

The study duration for an individual subject is approximately 7 months. Interim analysis for safety will be performed on the data that are collected from all study subjects at Visit 1, Visit 2 (1 day after Visit 1), Visit 3 (7 days after Visit 1), and Visit 4, while interim analysis for immunogenicity will be performed on the data that are collected from all study subjects at Visit 1 and Visit 4. Table 3 illustrates the schedule of activities (SOA) and timing of study visits and assessments.

**Table 3 T3:** Schedule of study visits and assessments—Visit 1 to Visit 5.

Visit number	Screening	1	2	3	4	5	Unplanned	Unplanned
Visit description	Screening	Vax 1	Next-Day Follow-up Visit (Vax 1)	1-Week Follow-up Visit (Vax 1)	1-Month Follow-up Visit	6-Month Follow-up Visit	Potential COVID-19 Illness Visit	Potential COVID-19 Convalescent Visit
Visit window (Days)	0 to 28 Days Before Visit 1	Day 1	1 to 3 Days After Visit 1	6 to 8 Days After Visit 1	28 to 35 Days After Visit 1	154 to 168 Days After Visit 1	Optimally Within 3 Days After Potential COVID-19 Illness Onset	28 to 35 Days After Potential COVID-19 Illness Visit
Physical examination (height, weight, BMI, vital signs, general appearance, examination of skin, auscultation of the heart, auscultation of the lungs, palpation of the abdomen, examination of extremities)	X	X	X	X	X	X		
ECG	X			X				
Collect blood sample for hematology and chemistry^a^	~13.5 ml	~13.5ml	~13.5 ml	~13.5 ml	~13.5 ml	~13.5 ml		
Collect screening blood sample for HIV, HBsAg, HBc Ab, and HCV Ab tests	X included in chemistry sample							
Perform alcohol test	X							
Perform drug panel test	X							
Perform serum pregnancy test (if appropriate)	X							
Perform urine pregnancy test (if appropriate)		X				X		
Urinalysis^a^	X	X				X		
Obtain nasal swab (mid-turbinate) for COVID-19	X	X^b^					X	
Collect non-study vaccine information	X	X	X	X	X	X		

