## Assignment of intervention: allocation

### Randomization {16}

When an individual is determined to be eligible to participate in the study, the subject will be enrolled in a computerized randomization system that assigns a designated subject ID to allocate them to receive either the COVID-19 pDNA vaccine or placebo using Interactive Response Technology (IRT). Each cohort will contain 14 subjects. At Visit 1, the first two subjects of each cohort will be randomized according to a separate randomization list. One subject will be randomized to placebo, and one subject will be randomized to the study treatment to ensure that at least one subject will receive the study vaccine. They will be monitored for 4 h, with each subject to be monitored for 60 min before proceeding to the next subject. The next four participants in each cohort will be vaccinated at least 48 h after the first 2 participants complete their visit 2 safety data review. They will also be observed for at least 4 h at the study site. Vaccination of the rest of the subjects in each cohort will commence no sooner than 24 h after the sixth participant has undergone vaccination. All subjects in the dosing visit (Visit 1) will be observed for 4 h.

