## Data collection and management

### Plan for assessment and collection of outcomes {18a}

Safety assessments will be performed by measuring the local and systemic solicited AEs, unsolicited AEs, SAEs, as well as safety laboratory data for the study subjects. In addition, tolerability will be assessed for the vaccine. Tolerability will be assessed by the dual (joint) evaluation of both reactogenicity and unsolicited AEs. The time point for all safety assessments is described in the SOA. For each cohort, the first two subjects will receive the study vaccine and will be monitored for adverse reactions (AEs or SAEs) within the first 4 h. The next four participants in each cohort may be vaccinated at least 48 h after the first two participants have completed their Visit 2 safety data review and completed 48 h post-vaccination and they will also be observed for at least 4 h after study intervention administration at the study site. Vaccination of the rest of the subjects in each cohort will commence no sooner than 24 h after the sixth participant has received their vaccination, after which the next four subjects will receive the study vaccine and will be monitored for 4 h. Then, 24 h following vaccination, the remainder of the study cohort will receive the vaccine and will be monitored for 4 h. All subjects receiving their study vaccine dose will be observed for 4 h. All assessments will be documented in the eCRF as well as the AE and SAE forms. Further, safety parameters included in the diary card for will be collected from each participant. The types of the symptoms, severity, and the treatments to reduce symptoms at home will be recorded the diary card by the participant. The diary card are collected and assessed by the physician at each visit as described in the SOA (Table 3).

Assessment of reactogenicity will be performed by measuring the percentage and frequency of subjects with solicited local and solicited systemic AEs up to 7 days after each vaccination. Assessment of AEs will be performed by measuring the percentage and frequency of subjects with unsolicited AEs for 30 days after vaccination. For all cohorts, AEs will be monitored for 30 days after Visit 1. Assessment of SAEs will be performed by measuring the percentage and the frequency of subjects with SAEs from the start of the study until completion.

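### A 3:1 allocation cannot be met with 14 per cohort or 42 overall; the article should state whole-number arm sizes, reconcile its sentinel and Table 1 text, and stop describing dose cohorts as randomised

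*Protocol article*

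**What the plan says.** **Ratio and size.** The Abstract states "The subjects will be randomized to receive either the investigational vaccine or placebo (Saline) at a 3:1 allocation ratio". Intervention description {11a} applies the ratio to each cohort: "In each cohort, 14 subjects will undergo the IM administration of vaccine or placebo (Saline) at a 3:1 allocation ratio". Randomization {16} confirms the cohort size ("Each cohort will contain 14 subjects") and Trial Design {8} the total ("In total, 42 healthy individuals will be enrolled in the study").

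**First two subjects.** Randomization {16} places them on a separate list: "One subject will be randomized to placebo, and one subject will be randomized to the study treatment". It gives no ratio or counts for the other 12. Plan for assessment and collection of outcomes {18a} says "For each cohort, the first two subjects will receive the study vaccine and will be monitored for adverse reactions".

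**Staging.** Table 1, in both rows that describe controlled vaccination, doses two subjects, then four, then a remainder given as n = 10.

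**Dose assignment.** Section {11a} says "Subjects will be randomized into three different dosing cohorts". Trial Design {8} says "Subjects will be enrolled at a 1:1:1 ratio in a dose-escalating manner to one of three cohorts". Table 1 and Composition of data monitoring committee {5d} both set 12–14 days and a committee review before the next cohort opens. Interim analysis {21} says the data through Visit 4 will be used to evaluate the optimal dosage for future trials.

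**The concern.** The allocation ratio sets the arm sizes, and 14 is not divisible by four. The 1:1 first pair moves the split further from 3:1. The two descriptions of that pair lead to different counts, and Table 1 implies a different cohort size.

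The arm counts are the denominators for the safety percentages, which are reported by cohort. They also fix how many placebo recipients are available for comparison. As written, a reader cannot tell from the article whether the trial plans 30 or 33 vaccinees, and 12 or 9 on placebo.

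The second issue is what is randomised. If cohorts fill one after another, dose follows enrolment time. Only vaccine versus placebo within a cohort can then be randomised. Calling the cohorts randomised gives the dose comparison a standing that the design does not provide, and that comparison informs the choice of dose for later trials.

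**Working it through.** **Inputs.** 14 per cohort ({11a}, {16}); 42 in total ({8}); 3:1 vaccine to placebo (Abstract, {11a}); first two subjects one vaccine and one placebo ({16}), or both on vaccine (literal reading of {18a}); Table 1 staging of 2, 4 and 10.

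**Step 1: the stated ratio.**
- Per cohort: 14 × 3/4 = 10.5 vaccine and 14 × 1/4 = 3.5 placebo.
- Overall: 42 × 3/4 = 31.5 and 42 × 1/4 = 10.5.

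Neither gives whole numbers, so the stated figure cannot be reproduced, even with the first pair ignored.

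**Step 2: splits that can be delivered with 14 per cohort.**

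| First two | Other 12 | Cohort | Ratio | Trial |
|---|---|---|---|---|
| 1:1 ({16}) | 9:3 (3:1) | 10:4 | 2.5:1 | 30:12 |
| 1:1 ({16}) | 10:2 (5:1) | 11:3 | 3.67:1 | 33:9 |
| 2:0 ({18a}, literal) | 9:3 (3:1) | 11:3 | 3.67:1 | 33:9 |

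The split of the other 12 is an assumption, because {16} does not state it. If those 12 were randomised at probability 0.75 without blocking, 10 vaccinees would still be the expected number. The chance of exactly 10 would be C(12,9) × 0.75⁹ × 0.25³ = 0.258.

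**Step 3: Table 1.** 2 + 4 + 10 = 16 per cohort, or 48 over three cohorts, against 14 and 42. With 14 per cohort the remainder after six is 8. At 16, exact 3:1 is possible as 12:4; with a 1:1 first pair that requires 11:3 among the other 14. If those 14 were instead split 3:1, the cohort would be 11.5:4.5, again not whole numbers.

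**Step 4: effect on precision.**
- Chance of seeing at least one event with a true rate of 10%, per dose: 1 − 0.9¹⁰ = 65.1% with 10 vaccinees; 1 − 0.9¹¹ = 68.6% with 11.
- Two-sided 95% exact upper limit with zero events, 1 − 0.025^(1/n): 30.8% for n = 10 and 28.5% for n = 11.
- The same limit for placebo, if pooled over cohorts: 26.5% for n = 12 and 33.6% for n = 9.

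Against the nominal 3:1, a 10:4 split differs by 0.5 subject per cohort and 1.5 over the trial.

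**Step 5: what is randomised.** Trial Design {8} enrols by escalation, and Table 1 and {5d} hold each new cohort until the previous one has been dosed, 12–14 days have passed and the committee has reviewed safety. A subject therefore cannot be randomly assigned among the three doses. The 1:1:1 in {8} can only describe equal cohort sizes. The sentence in {11a} does not fit this.

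**The case against.** The strongest reply is that this is rounding and loose wording. Half a subject per cohort changes no conclusion: the safety analysis is descriptive, no power calculation depends on the ratio, and percentages will be based on subjects actually dosed. That stands, and it limits the weight of the point.

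A reader might infer that the randomisation system cannot be programmed. The documents do not support that: a 1:1 list for the first two and a 9:3 list for the other 12 can be built, and 9:3 is exactly 3:1. What is wrong is applying 3:1 to all 14 and to all 42.

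A reader might take 10:4 as the planned split. It is the direct result only if {16} and 14 per cohort stand and the other 12 are at 3:1. A split of 11:3 is equally close to 10.5:3.5.

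A reader might also treat {18a} as a definite plan to vaccinate both of the first two. The same section speaks of the next four and the remainder receiving vaccine too. Taken literally, nobody would receive placebo, so the term may simply mean the blinded injection. Section {16} is the more specific text. Even so, the literal readings differ and yield different arm sizes.

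On dose, the rest of the article consistently describes escalation, and the stated objectives compare vaccine with placebo. A reader might infer that a randomised between-dose test is planned; {21} announces none. The error is one sentence, but it bears on how the optimal-dosage evaluation will be read.

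**Conclusion.** The point holds as a moderate correction. The 3:1 ratio is arithmetically impossible with 14 per cohort and with 42 overall; this rests on no assumption. The deliverable split is 10:4 per cohort and 30:12 overall if the first two are split 1:1 and the other 12 at 3:1. It is 11:3 and 33:9 if both of the first two receive vaccine and the other 12 are at 3:1. The Table 1 staging adds to 16 and conflicts with 14.

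The consequence for precision is small: about 3.5 percentage points in the chance of seeing a 10% event at a given dose, and 9 against 12 placebo recipients in total. The value of the correction lies in giving readers definite denominators.

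Separately, the statement that subjects are randomised into dose cohorts is wrong for a design that opens cohorts in sequence. Between-dose comparisons are non-randomised, and dose is confounded with time of enrolment.

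**What to change.** 1. State whole-number vaccine and placebo counts per cohort and overall, with the split for the first two subjects and for the remaining subjects. These are 10:4 and 30:12 if {16} and 14 per cohort stand and the other 12 are at 3:1. Correct the 3:1 statements in the Abstract and {11a} to match.
2. Reconcile {16} and {18a} on what the first two subjects of each cohort receive. This review does not say which text should prevail.
3. Reconcile the n = 10 in Table 1, in both rows, with 14 per cohort.
4. Replace the {11a} sentence on randomisation into dosing cohorts with wording that cohorts are enrolled sequentially and that subjects are randomised to vaccine or placebo within a cohort.
5. In {21}, describe the between-dose comparison behind the optimal-dosage evaluation as non-randomised.

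The cost is text and a check of the randomisation specification against the stated counts. If 14 per cohort stands, the total remains 42.
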